### Sample size justification

DREAMS aims to reduce HIV incidence among AGYW by 40%. In the absence of a robust estimate of HIV incidence among the target population, we used data from the *Sisters* programme and the MTN-020 Dapivirine vaginal ring trial to determine the required sample size [9, 30]. A cohort analysis of *Sisters* programmatic data estimated that HIV incidence was 10.8% (95%CI: 8.1–16.1) among FSW aged 18–25 years [9]. In the ASPIRE trial, HIV incidence among women aged 18 to 45 was 4.5 per 100 person-years in the placebo arm, 6.2 per 100 person years in the placebo arms in South Africa, 2.6 in Malawi, Uganda and Zimbabwe [30]. Relative to the target population in our study, women in the ASPIRE trial might have been at lower risk of HIV, with only 7% reporting transactional sex in the previous year. Based on these estimates and assuming individual-level analysis, we assume that incidence among YWSS in the absence of DREAMS+PrEP is between 5.0 and 8.0 new infections per 100 person-years. We also anticipate that, at the point of enrolment, 20% of YWSS will test HIV positive and that 30% of YWSS will be LTFU over the 24-month period. Based on these estimates, we will recruit 1200 YWSS in the DREAMS+PrEP sites and 1200 in non-DREAMS sites to have sufficient person-years of follow-up to have 80% power to detect a reduction of 40% or more in incidence after 24-months at the *p* = 0.05 level (Table 1).

**Table 1 Tab1:** Study power to detect a 30–50% reduction in HIV incidence in DREAMS+PrEP cohort compared to incidence in a comparison cohort with at least 690 YWSS followed up over 24 months (1500–1380 person-years follow-up/cohort)

HIV incidence in comparison cohort	Reduction in HIV incidence in DREAMS+PrEP cohort					
	50%	40%	30%	50%	40%	30%
	1500pyrs follow-up per cohort			1380pyrs follow-up per cohort		
5.0	94	77	49	92	75	46
6.0	96	85	59	96	82	55
7.0	98	90	66	98	87	62
8.0	99	93	72	99	91	67

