### Stages of primary outcome analysis

We will adopt a transparent and simple cohort approach to the analysis of the primary outcome. Our approach to inference will consider whether it is plausible that DREAMS+PrEP had an impact on HIV incidence among the target population [28, 29].

We will conduct our primary analysis in three phases. Each stage aims to build the strength of the evidence base of a plausible causal impact of DREAMS on HIV incidence. In phase one, we will take an individual-level cohort analysis approach. At 24-months, we will describe the number of women retained in the cohort and summarise follow-up time (average and total) in the DREAMS+PrEP and comparison sites. We will describe HIV incidence at 24 months in the DREAMS+PrEP and comparison groups with associated 95%CI. We will also describe site-specific estimates of incidence. Using Poisson regression, we will compare the incidence rates at 24-months across the two groups expressed as an unadjusted rate ratio with associated 95%CI presented. To account for the RDS design, we will weight the data by 1/self-reported degree of social network.

The unadjusted rate ratio is subject to confounding by risk factors for HIV that are differential across the two groups in the absence of random allocation and the small number of sites. In phase two, we will estimate a rate ratio adjusted for potential confounders. We will present the adjusted rate ratio with associated 95%CI.

In the third phase, we will assess whether there is evidence for an association between individual-level exposure to DREAMS+PrEP interventions and HIV incidence. For example, we will compare the risk of HIV infection between women self-reporting that they are adherent to PrEP and women who did not take PrEP. We will specify the exact measures of exposure after the year 1 data have been collected, without reference to the outcome data and before the final follow-up.

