We recognise that retention of the YWSS recruited into the cohorts may prove challenging, as such our sample size calculations assume a 30% LTFU over the 24-month study. Furthermore, individuals LTFU may differ in the two groups, leading to bias estimates of HIV incidence. We opted for a cohort design rather than repeat cross-sectional surveys as we are interested in the impact of DREAMS+PrEP among YWSS referred to and offered DREAMS+PrEP services. We recognise that both design options have limitations. Repeat cross-sectional surveys, however, would suffer from issues of temporality, we would not be able to explore individual-level changes over time, and women recruited at successive surveys may have had no exposure to DREAMS+PrEP. Through our cohort study design, YWSS will be referred to and offered DREAMS+PrEP services dependent on need. Our study will therefore allow us to understand women’s level of engagement and reasons for non-engagement with DREAMS.

The DREAMS package of interventions aims to reduce HIV incidence by 40% among AGYW. As such, our study is powered to detect a 40% difference in HIV between the DREAMS+PrEP and non-DREAMS comparison cohorts. This is a large reduction in incidence. If DREAMS+PrEP reduces incidence by 40% we may be able to detect this difference, if levels of LTFU and HIV prevalence at enrolment are as hypothesised, but reductions lower than 40% may not be detected with the proposed sample size. PrEP efficacy studies have shown up to 67% reduction in HIV among sero-discordant couples and young men and women in sub-Saharan Africa [1, 37, 38]. Sub-group analyses suggest efficacy is higher with increased levels of adherence [1, 37]. An offer of PrEP alongside interventions to support retention in or return to school, and improve access to HIV testing, STI screening and treatment among other services are likely to have a large impact on these women’s lives, their access to services and their risk of HIV infection. Should this study be underpowered, it can still provide evidence critical to understanding whether and how DREAMS+PrEP changed young women’s lives and to informing how to provide this underserved and vulnerable population with access to HIV prevention and care services within a broader social support package.

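### Table 1 and the 80% power sentence describe an unweighted comparison, but the phase-one primary rate ratio is weighted by 1/degree, so the stated power is not that of the planned analysis

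*Protocol article*

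**What the plan says.** Under Sample size justification, the calculation is introduced with "Based on these estimates and assuming individual-level analysis". Comparison-group incidence is taken to lie "between 5.0 and 8.0 new infections per 100 person-years". The other inputs are 20% HIV-positive at enrolment and 30% lost over 24 months. The plan is then that "we will recruit 1200 YWSS in the DREAMS+PrEP sites and 1200 in non-DREAMS sites", to "have 80% power to detect a reduction of 40% or more in incidence after 24-months". Table 1 gives power for reductions of 50%, 40% and 30%, with 1500 or 1380 person-years per cohort.

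Under Stages of primary outcome analysis, phase one estimates an unadjusted rate ratio by Poisson regression, and adds: "To account for the RDS design, we will weight the data by 1/self-reported degree of social network". The RDS diagnostics section also says that the analysis will account for network-based recruitment.

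The Discussion repeats that "our study is powered to detect a 40% difference in HIV between the DREAMS+PrEP and non-DREAMS comparison cohorts", and makes this conditional on loss to follow-up and on HIV prevalence at enrolment. Weighting is not named as a condition.

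**The concern.** Unequal weights reduce the effective number of events. If the weights are unrelated to the outcome, the variance of a weighted estimate is inflated by about 1 + CV² of the weights (the Kish factor). Self-reported network size usually varies between women, so its inverse varies too. If the power figures carry no allowance for this, they describe a more precise analysis than the one planned.

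The margin above 80% in Table 1 is thin over part of the assumed incidence range, so even a modest design effect could remove it. A reader of the Discussion would conclude that 80% power is secure once retention and prevalence turn out as assumed. The weighted analysis has not been shown to have that power.

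**Working it through.** **Inputs, all from Sample size justification.** Comparison incidence 5, 6, 7 or 8 per 100 person-years; rate ratio 0.60; 1500 or 1380 person-years per cohort; significance level 0.05. Sidedness is not stated; two-sided reproduces the table.

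**Step 1: reproduce Table 1.** Let e0 = person-years × rate and e1 = 0.6 × e0. With design effect DE,

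power = Φ( |ln 0.6| / √(DE × (1/e0 + 1/e1)) − 1.96 ), where |ln 0.6| = 0.511.

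Example at 6 per 100 and 1500 person-years with DE = 1: e0 = 90, e1 = 54, 1/90 + 1/54 = 0.0296, standard error 0.172. Then 0.511/0.172 = 2.97 and Φ(2.97 − 1.96) gives 84.3%; the table prints 85.

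| Power (%) for a 40% reduction | 5 | 6 | 7 | 8 |
|---|---|---|---|---|
| 1500 py, computed, DE = 1 | 77.3 | 84.3 | 89.4 | 92.9 |
| 1500 py, printed | 77 | 85 | 90 | 93 |
| 1380 py, computed, DE = 1 | 73.8 | 81.2 | 86.7 | 90.8 |
| 1380 py, printed | 75 | 82 | 87 | 91 |

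All 24 cells of the table, including those for 50% and 30%, agree within 2 points. No allowance for weighting is hidden in the figures.

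**Step 2: how much design effect can the plan absorb?** Setting power to 80% (1.96 + 0.84 = 2.80) and solving:

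largest DE = (0.511/2.80)² / (1/e0 + 1/e1) = 0.0332 / (1/e0 + 1/e1).

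At 6 per 100 and 1500 person-years: 0.0332/0.0296 = 1.12.

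| Largest DE keeping 80% power | 5 | 6 | 7 | 8 |
|---|---|---|---|---|
| 1380 py | 0.86 | 1.03 | 1.20 | 1.38 |
| 1500 py | 0.94 | 1.12 | 1.31 | 1.50 |

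This step uses only the article's own figures. Values below 1 at 5 per 100 mean that 80% is missed without any weighting, as Table 1 itself prints (75 and 77).

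**Step 3: illustration under assumed design effects.** The article gives no degree distribution, so these values are assumptions. For orientation, log-normal degree with log-SD 0.5, 0.7 or 0.9 gives a Kish factor exp(SD²) of 1.28, 1.63 or 2.25.

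| Power (%), 1380–1500 py | 5 | 6 | 7 | 8 |
|---|---|---|---|---|
| DE 1.25 | 64–68 | 72–76 | 79–82 | 84–87 |
| DE 1.5 | 56–60 | 64–68 | 71–74 | 77–80 |
| DE 2.0 | 45–48 | 52–56 | 59–62 | 64–68 |

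Solving the same formula for the rate ratio at 80% power, the detectable reduction at DE 1.5 runs from about 40% (8 per 100, 1500 person-years) to about 51% (5 per 100, 1380 person-years).

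**The case against.** Several points on the other side are sound.

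- Table 1 is not miscalculated, and the section states openly that it assumes individual-level analysis. The fault is an omitted allowance, not an arithmetic error.
- The size of the loss rests on assumed design effects. The Kish factor is itself approximate: it takes the weights as unrelated to the outcome, whereas network size may be related to HIV risk. It also leaves out correlation within recruitment chains, which would normally lower power further.
- Weighting is stated explicitly only for the phase-one unadjusted ratio. The article does not say whether the phase-two adjusted ratio is weighted.
- Inference is to rest on plausibility built over three phases with a process evaluation. The Discussion also concedes that reductions below 40% may be missed and that the study might be underpowered. This softens the consequence of a null result.

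One might reply that variance handling belongs in the later analysis plan. That does not answer the point, because the article itself fixes both the power figure and the weighting, and the two do not match. Nor does the Discussion's caveat cover it, since the only conditions it names are retention and prevalence.

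A reader might infer that 80% power holds only if degree hardly varies. The figures do not support that in general. At 8 per 100, design effects of 1.38–1.50 are tolerable, which correspond to a CV of the weights of √0.38 = 0.62 to √0.50 = 0.71. At 7 per 100 the corresponding CVs are 0.45 to 0.56. Only at 6 per 100 is there almost no room. A reader might also attribute the shortfall at 5 per 100 to the weighting. It is already printed in Table 1 and is a separate point.

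**Conclusion.** The mismatch stands: the stated power belongs to an unweighted comparison, and the phase-one primary rate ratio is weighted by 1/degree. Within the article's assumed incidence range, the design effect at which 80% power for a 40% reduction is lost is 1.03–1.12 at 6, 1.20–1.31 at 7 and 1.38–1.50 at 8 per 100 person-years. These limits rest on a two-sided 5% Wald test of the log rate ratio and on 1380–1500 person-years per cohort.

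Whether the real design effect exceeds these limits cannot be settled from the article, so it does not follow that the study is underpowered. What follows is that 80% power has not been shown for the analysis planned. No estimate is biased by this; the point concerns the stated power only.

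**What to change.** Keep the sample size. Then:

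1. Restate Table 1 and the power sentence for the weighted analysis over a stated range of design effects, for example 1.0, 1.5 and 2.0, with the reduction detectable at 80% power for each.
2. Once enrolment is complete, replace the assumed value with the Kish factor computed from the degrees reported at enrolment. This needs no outcome data. Say that it is approximate and omits correlation within recruitment chains.
3. In the Discussion, add the variation of the weights to loss to follow-up and prevalence as a condition on power.

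The cost is a recalculated table and a few sentences, with no additional participants. The only downside is a less favourable stated power.

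### The 80% power claimed for a 40% reduction fails at the bottom of the plan's own incidence range: Table 1 gives 77% and 75% at 5.0 per 100 person-years

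*Protocol article*

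**What the plan says.** In the protocol article, under Sample size justification, the inputs are these:

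- Comparison incidence: "we assume that incidence among YWSS in the absence of DREAMS+PrEP is between 5.0 and 8.0 new infections per 100 person-years".
- Losses: "20% of YWSS will test HIV positive and that 30% of YWSS will be LTFU over the 24-month period".
- Enrolment: "we will recruit 1200 YWSS in the DREAMS+PrEP sites and 1200 in non-DREAMS sites".

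From these the text concludes that the study has "80% power to detect a reduction of 40% or more in incidence after 24-months", at the 0.05 level, and refers to Table 1. The claim is not restricted to any part of the incidence range.

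Table 1 gives power for incidences of 5.0, 6.0, 7.0 and 8.0, under 1500 and 1380 person-years per cohort. Its title describes "at least 690 YWSS followed up over 24 months". For a 40% reduction the entries are:

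| Incidence per 100 person-years | 1500 person-years | 1380 person-years |
|---|---|---|
| 5.0 | 77 | 75 |
| 6.0 | 85 | 82 |
| 7.0 | 90 | 87 |
| 8.0 | 93 | 91 |

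The Discussion repeats that "our study is powered to detect a 40% difference in HIV between the DREAMS+PrEP and non-DREAMS comparison cohorts". It makes detection depend on loss to follow-up and HIV prevalence at enrolment, and does not mention incidence.

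**The concern.** A power statement that rests on a range of incidence and carries no condition should hold across that range. Here it fails at the lower limit in both person-year scenarios of the table it cites. The 40% reduction is the programme's target and 80% is the headline design figure for the primary outcome. At 5.0, the plan's own table implies a 23–25% chance of missing a true 40% reduction, where the text tells the reader 20%.

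The lower limit cannot be set aside. The section says that no robust incidence estimate exists for this population. One of its two sources, the dapivirine ring trial, had placebo-arm rates of 4.5 overall and 2.6 in the group of countries that includes Zimbabwe, although the plan notes that those women may have been at lower risk.

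A second, smaller mismatch lies in the table title: the number of women it gives as a minimum is more than the stated losses leave.

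**Working it through.** **Inputs (all from the Sample size justification).** Comparison rate λ₀ = 0.05 to 0.08 per person-year; rate ratio 0.60, so λ₁ = 0.6λ₀; equal person-years PY per cohort, 1500 or 1380; significance level 0.05; individual-level analysis with no design effect. Sidedness is not stated. Two-sided is assumed because it reproduces the table.

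**Step 1: reproduce Table 1.** Two-rate Poisson comparison:

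power = Φ( (λ₀ − λ₁) / √((λ₀ + λ₁)/PY) − 1.96 )

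- 5.0, PY = 1500: 0.02/√(0.08/1500) = 2.739; Φ(0.779) = 78.2%. Table: 77.
- 5.0, PY = 1380: 0.02/√(0.08/1380) = 2.627; Φ(0.667) = 74.8%. Table: 75.
- 6.0, 7.0, 8.0, PY = 1500: 85.1, 90.0, 93.4%. Table: 85, 90, 93.
- 6.0, 7.0, 8.0, PY = 1380: 82.1, 87.5, 91.4%. Table: 82, 87, 91.

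Over all 24 cells, 22 agree within 2 points. The other two (30% reduction at 5.0) differ by 2.1 and 2.3. The 77 and 75 are therefore not misprints.

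**Step 2: does the choice of formula or sidedness explain the 80%?** The log rate ratio version, Φ(−ln 0.6/√(1/e₀ + 1/e₁) − 1.96), gives 77.3% at 1500 (e₀ = 75, e₁ = 45 events) and 73.8% at 1380 (69 and 41.4). Eight formula variants range from 76.7% to 81.5% at 1500 and from 73.2% to 78.3% at 1380. The only one above 80%, an uncorrected two-proportion test on doubled rates, misses the printed 77 by 4.5 points. A one-sided 0.05 test gives Φ(2.739 − 1.645) ≈ 86% and Φ(2.627 − 1.645) ≈ 84%, which does not match the table either.

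**Step 3: incidence at which power reaches 80%.** Setting the Step 1 expression to 80% requires (1.96 + 0.8416)² = 7.849 = 0.16λ₀PY/1.6, so λ₀ = 78.49/PY.

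- PY = 1500: 5.2 per 100 person-years (log rate ratio: 5.35).
- PY = 1380: 5.7 (log rate ratio: 5.8).

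At 5.0, the Step 1 formula needs 78.49/0.05 ≈ 1570 person-years per cohort, more than either scenario.

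**Step 4: number of women.** 1200 × 0.80 × 0.70 = 672, against 690 in the title: a gap of 18 women, or 2.6%. To have 690, loss would have to be 1 − 690/960 = 28.1%, or enrolment 690/0.56 ≈ 1232 per group. Since 690 × 2 = 1380, the lower scenario looks like completers at two full years each. The same count with 672 is 1344 person-years, with power 73.6% at 5.0, about 1 point below 74.8%.

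**Step 5: person-years from women lost.** Under Primary outcome measurement, a woman lost to follow-up is censored at her last negative test, so one lost after a negative 12-month test still contributes time. Of the 960 HIV-negative women, 288 are expected to be lost. Before any time is cut short by seroconversion:

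- 36 of the 288 (12.5%) giving one year each takes 1344 to 1380.
- 156 of the 288 (54%) takes it to 1500.
- An average of half a year from all 288 gives 1488 person-years (77.9% at 5.0).
- One year from all 288 gives 1632 (81.5%).

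**The case against.** The strongest reply is that the shortfall is small and in plain view. It is 3 to 5 points in one of four rows, the sentence points to the table that shows it, and every 40% entry from 6.0 to 8.0 lies between 82% and 93%. The programme data gave an incidence of 10.8% (95% CI 8.1–16.1) among young sex workers, so 5.0 is a cautious floor. The Discussion says only that a 40% difference may be detectable, and allows that the study could prove underpowered. All of this stands and limits the weight of the point. It does not make the unconditional sentence true.

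A reader might also infer more than the document supports:

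- *That 1380 should be replaced by 1344 person-years.* This would give every lost woman zero time, against the plan's own censoring rule. Step 5 shows that 1380–1500 is plausible. What is missing is the assumption behind it.
- *That the cells are too high because a seroconverter's time stops at the mid-point between tests.* The columns are indexed by person-years, however these accrue. Truncation affects how many women are needed to reach a column, not the power within it.
- *That 80% holds only from 6.0.* That is the first tabulated row that meets it. By calculation the crossing is lower, and it depends on the person-years.
- *That a null result will be read as excluding a 40% effect.* The plan bases inference on plausibility and on rate ratios with 95% confidence intervals, and nothing in it commits to such a reading.

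**Conclusion.** Wrong as written. The unconditional 80% is contradicted by the plan's own Table 1 at 5.0 per 100 person-years: 77% with 1500 person-years and 75% with 1380. The table is right and the sentence needs to change. The claim is met in every tabulated row from 6.0 upward, and by calculation from about 5.2–5.4 (1500) or 5.7–5.8 (1380).

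This rests on a two-sided 0.05 test, an individual-level analysis without design effect, and the person-years that the table assumes. If every lost woman contributed a full year, power at 5.0 could pass 80%, but the article states no such assumption and its more generous scenario still prints 77%.

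The difference between 690 and 672 women is a genuine but minor inconsistency, worth about 1 point of power. Neither point shows that enrolment is too small for the rest of the assumed range.

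**What to change.** With enrolment unchanged:

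1. In the Sample size justification, replace the flat claim with wording such as: *75–77% power for a 40% reduction at 5.0 per 100 person-years, and at least 82% at 6.0 or above (Table 1).*
2. In the Discussion, add comparison-group incidence to loss to follow-up and enrolment prevalence as a condition of the power statement.
3. In the Table 1 title, change 690 to 672, or state the retention assumption that yields 690 (about 28% loss).
4. Add one sentence giving the partial follow-up expected from women lost after a negative 12-month test, which is what supports 1380–1500 person-years. Keep both columns; do not substitute 1344.

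The cost is two reworded sentences, one caption edit and one added sentence. No cell of Table 1 needs recomputing, and the headline power becomes slightly less favourable at the lowest incidence.

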### Process evaluation

Embedded within the impact evaluation is a process evaluation that will compile routine programme data and conduct qualitative research to assess the fidelity, acceptability, and feasibility of the DREAMS+PrEP package. The process evaluation framework is designed to accompany the assumed pathway of the intervention (Fig. 2). The aim of the process evaluation is to strengthen the plausibility that any apparent effect is attributable to the DREAMS combined package.

**Fig. 2 Fig2:**
[figure not shown]
Hypothesised causal pathway of the DREAMS+PrEP package of interventions on HIV incidence

### Methods

To determine fidelity, interviews with staff across DREAMS providers will examine whether the programme components were delivered as intended and identify challenges, delays, or omissions in planned implementation. We will also conduct in-depth interviews at the time of the network-based recruitment with five “seeds” in each of the two DREAMS+PrEP and two non-DREAMS sites to discuss issues relevant to the hypothesised causal pathway. In-depth interviews will also be conducted in these four sites with a cross-section of twenty-four (*n* = 24) participants every six-months, purposively sampled according to age and levels of uptake of different DREAMS+PrEP intervention or *Sisters* programme components. Twice a year, participatory evaluation workshops will be conducted with YWSS engaged in DREAMS+PrEP to elucidate their perceptions of the quality and usefulness of different aspects of the programme. Records of outreach contacts, activity attendance and referrals between implementing partners will be analysed to assess the number of DREAMS services that YWSS access, and with what frequency. Finally, a smaller cohort of YWSS will be prospectively followed through repeat interviews and audio diaries (*n* = 12) to explore dimensions of their lives targeted by DREAMS, namely empowerment, financial literacy, personal aspirations, and sexual behaviour and health at individual level, and social support and peer norms at community level.

